### Study instruments

There are four study instruments are used in this study, one to evaluate the structure of care and three to evaluate the PRO (Kidney Disease Quality of Life (KDQOL-36), the PEI and the GRS). Evaluation of the process and outcomes of care do not involve the use of study instruments as the necessary data are retrieved from the HA computerized medical record system by the Statistics and Workforce Planning Department.

#### Structure of care questionnaire [Additional file 2- SOC questionnaire]

Structure of care questionnaires are sent to the doctor and nurse in-charge of the HD-PPP programme at each study site for completion. The questionnaire seeks to characterize the attributes of the setting in which the health care service is delivered, including the human resources and training (staff); the hardware needed (space, facilities, and data collection); and the organization and management of the programme.

#### Kidney Disease Quality of Life (KDQOL-36)

KDQOL-36 survey is a kidney disease specific measure of health related quality of life [12]. It comprises generic and disease-specific cores. The generic core is the Short Form-12 Health Survey (SF-12). The SF-12 is a generic HRQOL measure, which can be summarized into physical and mental component summary (PCS and MCS) scores. The SF-12 has been validated for use in Hong Kong [13]. The disease-specific core has 3 subscales (4 items for burden of kidney disease; 12 items for symptom bother and problems and 8 items for effects of kidney disease). The domain scores are calculated by summation of the relevant item scores and transformation into a range from 0 to 100, with higher scores indicating better HRQOL.

#### The Patient Enablement Instrument (PEI)

PEI will be used to measure patient’s enablement in coping with the illness and life [14]. It has 6 items and each rated on a 3-point scale (0 = the same or less; 1 = slightly improved/increased; 2 = greatly improved/increased). The summation of the item scores gives the PEI score with a higher score indicating better enablement. The PEI has been translated into Chinese and shown to be valid and reliable in the general Chinese population [15].

#### The Global Rating Scale (GRS)

GRS, adapted from studies [16, 17], will be used to assess the subject’s global perception of any change in their overall health condition on a 7-point scale (−3 = much worse to 3 = much improved, with 0 = no change) over the past 12 months.

### Data analysis

Descriptive statistics on standard of care will be calculated including the percentage of centres meeting each structure criterion, percentage of subjects enrolled, dropped out, receiving criterion process including HD, and percentage of subjects achieving each outcome criterion.The difference in clinical and PRO of patients who take part in the HD-PPP programme at baseline, 12, 24, 36 and 48 months will be compared by paired sample t-tests.Independent sample t-test or chi-square test as appropriate will be used to compare the clinical outcomes between HD-PPP participants and control patients.Independent sample t-test or chi square test as appropriate will be used to compare the clinical outcomes between results achieved in different evaluation cycles.

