### Hypotheses

The following hypotheses will be tested:The criteria on structure and process should be achieved by all participating HA renal units and community HD centres;The dialysis for patients should be adequately maintained (Kt/V ≥ 1.2 for patients receiving 3 HD sessions per week or ≥ 1.8 for those receiving 2 HD sessions per week) after 12, 24, 36 and 48 months in the programme;Patients in the programme should report no worse outcomes as patients managed by usual care in the HA (control);

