#### Secondary

Clinical outcomes include dialysis adequacy and blood haemoglobin.Patient reported outcomes (PRO) are measured by the change in Short Form-12 version 2 (SF-12v2) scores, the Patient Enablement Instrument (PEI) and Global Rating Scale (GRS) scores at baseline and after 12 months.

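### Within-programme change in dialysis adequacy is assigned a paired t-test only, although adequacy is a yes/no status with cut-offs that depend on session frequency

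*Protocol article*

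**What the plan says.** All references are to the protocol article.

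- **Hypotheses.** Adequacy is defined as "Kt/V ≥ 1.2 for patients receiving 3 HD sessions per week or ≥ 1.8 for those receiving 2 HD sessions per week" and is to be maintained "after 12, 24, 36 and 48 months in the programme".
- **Outcome measures.** The proportion of patients with adequate HD is a primary outcome. Under Secondary, "Clinical outcomes include dialysis adequacy and blood haemoglobin", with no statement of the scale on which adequacy is then analysed. The Discussion (Potential to realize change) calls Kt/V the primary clinical outcome indicator.
- **Data analysis, within the programme.** Clinical and patient-reported outcomes "at baseline, 12, 24, 36 and 48 months will be compared by paired sample t-tests".
- **Data analysis, the other comparisons.** Against controls: "Independent sample t-test or chi-square test as appropriate will be used to compare the clinical outcomes between HD-PPP participants and control patients". Between cycles: "Independent sample t-test or chi square test as appropriate will be used to compare the clinical outcomes between results achieved in different evaluation cycles". Descriptively, the section plans the "percentage of subjects achieving each outcome criterion".
- **Background and Subjects.** The frequency of dialysis is overseen by each patient's hospital nephrologist. Controls are matched on age and gender. No section stratifies or adjusts for session frequency.

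**The concern.** The sentences on controls and on cycles each leave a choice between a test for means and a test for proportions. The within-programme sentence does not. It covers the comparison over time closest to the claim that adequacy is maintained, and it names a test for mean differences when the primary outcome is a status.

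The sentence can be carried out in two ways, and neither is satisfactory. On Kt/V itself, the values are not on one scale, because the plan judges the same number differently at 2 and at 3 sessions a week. On the status coded 0/1, the test is an approximation to the paired binary test that the plan does not name.

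At stake is a reported within-programme trend in the primary clinical indicator that could point the opposite way from the proportion of patients who are adequate.

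**Working it through.** The plan states no sample size, SD, adequacy rate or session mix for this point, so there is no figure of its own to reproduce. The cut-offs are taken as given.

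**1. Does Kt/V rank adequacy across frequencies?** Inputs are the cut-offs in the Hypotheses section: 1.2 at 3 sessions, 1.8 at 2 sessions.

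- Before: Kt/V 1.6 on 2 sessions. 1.6 < 1.8, inadequate.
- After: Kt/V 1.3 on 3 sessions. 1.3 ≥ 1.2, adequate.
- Contribution to a paired t-test on Kt/V: 1.3 − 1.6 = −0.3.

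The patient moves from inadequate to adequate and is scored as a deterioration. Relative to the cut-off in force at each visit, the same change is 1.6/1.8 = 0.89 to 1.3/1.2 = 1.08, a rise across 1.

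The distortion needs a change of frequency within the patient. For a patient who stays on the same frequency, both values are judged by one cut-off and the direction of change is right.

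**2. How far can a shift in frequency move the mean?** Assumed: Kt/V is normal with SD 0.25 within each frequency, with mean 1.4 on 3 sessions and 1.7 on 2 sessions. With share p on 2 sessions:

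- mean = (1 − p) × 1.4 + p × 1.7
- adequate = (1 − p) × P(Kt/V ≥ 1.2 on 3 sessions) + p × P(Kt/V ≥ 1.8 on 2 sessions)

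| Share on 2 sessions | Mean Kt/V | Adequate |
|---|---|---|
| 80% | 1.64 | 43.3% |
| 60% | 1.58 | 52.2% |
| 40% | 1.52 | 61.1% |
| 20% | 1.46 | 69.9% |

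In a cohort measured at both visits, the mean paired difference equals the difference of the two means. A shift from 80% to 20% on 2 sessions therefore gives 1.46 − 1.64 = −0.18, while adequacy rises by 69.9 − 43.3 = 26.6 percentage points.

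With assumed means 1.4 and 2.0 instead, 78.8% are adequate at every mix, yet the mean goes from 1.88 at 80% on 2 sessions to 1.52 at 20%. Each 10-point shift in the mix moves the mean by 0.10 × 0.3 = 0.03 in the first case and 0.10 × 0.6 = 0.06 in the second. With no shift the effect is zero.

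**3. What if the 0/1 status is tested?** Let b patients change in one direction and c in the other, out of n.

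- Paired t: d = (b − c)/n, s² = [(b + c) − (b − c)²/n]/(n − 1), t = d/√(s²/n)
- McNemar, uncorrected: (b − c)²/(b + c) on 1 df
- Exact McNemar: two-sided binomial test of b out of b + c at 0.5

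For assumed n = 120, b = 18, c = 8: d = 10/120 = 0.083; s² = (26 − 100/120)/119 = 0.211; t = 1.98. McNemar is 100/26 = 3.85.

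| n | b v c | Paired t, p | McNemar, p | Exact McNemar, p |
|---|---|---|---|---|
| 120 | 18 v 8 | 0.0494 | 0.0499 | 0.0755 |
| 120 | 12 v 4 | 0.0450 | 0.0455 | 0.0768 |
| 120 | 8 v 2 | 0.0575 | 0.0578 | 0.1094 |
| 60 | 8 v 2 | 0.0571 | 0.0578 | 0.1094 |
| 30 | 5 v 0 | 0.0226 | 0.0253 | 0.0625 |

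The paired t-test follows uncorrected McNemar closely. It is more liberal than the exact test, most clearly with few discordant pairs. The n of 120 is borrowed from cumulative enrolment at 31 March 2012 (Discussion); recruitment ran to 30 June 2014, so the final n is not known from the article.

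**The case against.** The best defence is that the plan already handles adequacy properly in most places. The percentage meeting each outcome criterion is planned, and it answers directly whether patients meet the threshold at 12 to 48 months. Chi-square is available against controls and between cycles. The paired t-test suits haemoglobin and the quality-of-life scores, which the same sentence covers. An article may leave the analysed scale to a fuller document. All of this stands, and it limits the point to one sentence.

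Three stronger readings are tempting and are not supported.

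- *That clinical outcomes are analysed by t-tests throughout.* The Data analysis section says otherwise for two of its three comparisons.
- *That the plan commits to pooling raw Kt/V over 2 and 3 sessions.* No sentence says so. It can be inferred, since a t-test needs a mean and adequacy is listed under both primary and secondary outcomes, but the scale is left open.
- *That the comparison with controls is biased by a known amount.* One could place everyone at the cut-off with 30% v 60% on 2 sessions and obtain means of 0.3 × 1.8 + 0.7 × 1.2 = 1.38 and 0.6 × 1.8 + 0.4 × 1.2 = 1.56. That mix is invented, and a chi-square test on status would show no difference. The problem there arises only if a t-test is chosen for pooled raw Kt/V.

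What the defence does not remove is that the within-programme sentence fixes a test, gives no alternative, and applies it to the primary clinical indicator.

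**Conclusion.** The point holds for the within-HD-PPP comparison over time. The named test is wrong in kind for the binary status, with small numerical consequence unless discordant pairs are few. On per-session Kt/V it can point the wrong way when patients change frequency.

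The direction of that error follows from the plan's own cut-offs and needs no assumption. Its size does: the shift of −0.18 against a gain of 26.6 points in adequacy rests on assumed means, an assumed SD and a large assumed shift in frequency. The article leaves frequency to the nephrologist and does not say how often it changes. The planned percentages would still describe the adequacy hypothesis correctly; the risk is a significance test beside them that contradicts them.

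This should be corrected before the within-programme comparisons are analysed, but it does not undermine the plan as a whole.

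**What to change.** In the Data analysis section:

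1. Test within-programme change in adequacy on the status defined in the Hypotheses section, using the patient's session frequency at that visit. Use McNemar for a pair of visits (exact when discordant pairs are few), or a repeated-measures logistic model over all visits.
2. State that comparisons with controls and between cycles use the same status, by chi-square or logistic regression.
3. Analyse continuous Kt/V only within session-frequency strata, or as Kt/V divided by the plan's cut-off for the patient's frequency at that visit. The two cut-offs give the same product with sessions (3 × 1.2 = 2 × 1.8 = 3.6), so the ratio ranks patients as sessions × Kt/V would. The plan itself defines no weekly sum, and the ratio does not need one.
4. Keep paired t-tests for haemoglobin and the quality-of-life scores.

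The cost is a few sentences. No new data item is required, because adequacy cannot be scored without session frequency.

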The target population for the HD-PPP programme include existing HA patients who fulfill the designated clinical criteria and are currently receiving HD in HA hospitals, new ESRD patients with contraindications for PD or patients who are currently on PD but are at risk of treatment failure. Eligible patients who choose to enroll in the programme will receive HD treatment in their selected community HD centre run by a private or charitable organization, and will pay no additional fees. The frequency of dialysis and other medical decisions would be overseen by the HA nephrologist looking after that particular patient. HD-PPP participants are followed up regularly at the renal specialist outpatient clinic (SOPC) to monitor their HD adequacy, renal function and other relevant clinical parameters.

As part of the development of a new health care service programme, it is important to include an evaluation component, best undertaken by an independent third party working in close collaboration with the programme planners, providers and administrators, to examine whether the programme delivers the care that it is intended to deliver, to the desired standard. The effectiveness of the programme in benefitting the health of service recipients and the sustainability of the programme can also be determined over a longer period of time. Such findings will provide valuable evidence to help those providing front-line care as well as those developing and coordinating the programme to improve the quality of patient care, and to support the continued funding and expansion of the programme.

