### Subjects

All patients participating in the HD-PPP programme between 1 March 2010 and 30 June 2014 will be included in the evaluation on process of care. All HD-PPP participants and an equal number of non-HD-PPP participants (eligible for HD-PPP but not participating) matched by age and gender will be included in the evaluation on the outcomes of care. The non-HD-PPP subjects will be selected from the HA patient database by the HA Statistics and Workforce Planning Department. Subjects will be recruited via a letter from the HA or on-site by HKU research assistants upon enrolment in the HD-PPP programme.

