#### Evaluation on outcomes of care

Anonymized data on clinical parameters at baseline, 12, 24, 36, 48 and 60 months after enrollment will be retrieved from the CMS by the HA statistics team.

For patient-reported outcomes, HD-PPP subjects and non-HD-PPP subjects will be invited in person at the community centre/renal unit to complete a telephone/face-to-face survey on health-related quality of life at enrolment into the HD-PPP (or equivalent time for non-HD-PPP), and then again at 12, 24, 36, 48 and 60 months. The follow up surveys will also include questions assessing patient enablement and global rating of change in health condition. The trained research assistant administering the patient-reported outcomes questionnaire survey will also obtain written informed consent from each patient prior to commencing the survey.

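### The HD-PPP versus control comparison of clinical outcomes is fixed as an unadjusted test, although enrolment is by choice and controls are matched only on age and gender

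*Protocol article*

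**What the plan says.** The Data analysis section states the test outright: an independent-sample t-test or a chi-square test, whichever suits the outcome, is to "compare the clinical outcomes between HD-PPP participants and control patients". It names no covariate, baseline term, matched analysis or site term. It gives no between-group test for patient-reported outcomes (PROs). Baseline appears there only in paired t-tests within HD-PPP participants.

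The comparison is not randomised. The Background describes entry by choice: "Eligible patients who choose to enroll in the programme". Under Subjects, the outcome evaluation adds "an equal number of non-HD-PPP participants (eligible for HD-PPP but not participating) matched by age and gender". Besides patients already on HD in public hospitals, the target population includes "new ESRD patients with contraindications for PD or patients who are currently on PD but are at risk of treatment failure".

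On baseline data, the section Evaluation on outcomes of care plans the PRO survey for both groups "at enrolment into the HD-PPP (or equivalent time for non-HD-PPP), and then again at 12, 24, 36, 48 and 60 months". For clinical data it says "Anonymized data on clinical parameters at baseline, 12, 24, 36, 48 and 60 months after enrollment will be retrieved from the CMS", without mentioning controls.

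The comparison serves the third hypothesis, that participants report outcomes no worse than usual-care controls. The second hypothesis sets the Kt/V standard by frequency: at least 1.2 with three sessions a week, at least 1.8 with two.

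**The concern.** Matching on age and gender balances those two factors only. Entry route, weekly sessions and baseline health are left free to differ between those who enrolled and those who did not, and each can affect later Kt/V, haemoglobin or quality of life. An unadjusted test attributes any such difference to the programme.

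For a no-worse claim this can go either way. If healthier patients move to community centres, the programme can look acceptable despite poorer care. If sicker patients move, a sound programme can look deficient. The Discussion says the evaluation is meant to inform decisions on continuing and expanding the programme.

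The independent-sample tests also treat patients as unrelated, although they are treated at 15 renal units and 7 community centres (Partnership approach). That can make standard errors too small.

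**Working it through.** The article states no sample size, power, margin or effect size, so there is no design figure to reproduce. What follows is illustration.

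**Inputs from the article.** 120 patients ever enrolled by 31 March 2012 (Discussion); equal numbers of controls (Subjects); 7 community centres and 15 renal units (Partnership approach). Inclusion runs to 30 June 2014, so the final number may be larger.

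**Assumed inputs.** Two-sided 5% level, normal approximation, no true programme effect, unit SD, baseline-to-follow-up correlation ρ of 0.3 to 0.7, baseline imbalance of 0.2 or 0.3 SD, site ICC of 0.01 to 0.10, patients spread evenly over sites.

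**1. Confounding, if follow-up levels are compared.** Bias = imbalance × ρ. SE = √(2/120) = 0.129 SD. The rejection rate is the chance that |Z| exceeds 1.96 when Z is centred at bias/SE.

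| Imbalance (SD) | ρ | Bias (SD) | False-positive rate |
|---|---|---|---|
| 0.2 | 0.3 | 0.06 | 7.5% |
| 0.2 | 0.5 | 0.10 | 12.1% |
| 0.2 | 0.7 | 0.14 | 19.2% |
| 0.3 | 0.3 | 0.09 | 10.7% |
| 0.3 | 0.5 | 0.15 | 21.3% |
| 0.3 | 0.7 | 0.21 | 37.0% |

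A larger sample would not remove the bias. It would make the same bias significant more often.

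**2. Kt/V and session frequency.** The two standards differ by 1.8 − 1.2 = 0.6. If every patient sat exactly on the relevant standard, each percentage-point difference between groups in the share on two sessions would shift the difference in mean Kt/V by 0.6/100 = 0.006, with no difference in adequacy. A t-test on Kt/V cannot separate this from quality of care.

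**3. Site clustering.** Design effect = 1 + (m − 1) × ICC, with m = 120/7 = 17.1 for HD-PPP and m = 120/15 = 8 for controls. The variance of the contrast is inflated by the average of the two. True size = 2 × [1 − Φ(1.96/√average)].

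| ICC | HD-PPP | Controls | Average | True size of nominal 5% |
|---|---|---|---|---|
| 0.01 | 1.16 | 1.07 | 1.12 | 6.4% |
| 0.05 | 1.81 | 1.35 | 1.58 | 11.9% |
| 0.10 | 2.61 | 1.70 | 2.16 | 18.2% |

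**4. Matching.** If matching were pairwise with within-pair correlation r of 0.05, 0.10 or 0.20, the independent test would have true size 2 × [1 − Φ(1.96/√(1 − r))] = 4.4%, 3.9% or 2.8%. That is conservative.

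**5. Gain from baseline adjustment.** Residual variance falls to 1 − ρ² = 91%, 75% or 51% at ρ = 0.3, 0.5 or 0.7. If the linear model holds and baseline is measured without error, the bias from imbalance in that baseline is removed.

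**The case against.** Controls must be eligible for the programme, so both groups come from the eligible population. The Discussion also reports a waiting list for places, so some non-participation may reflect capacity and not choice. This stands: the groups can differ, but the article does not show that they do.

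Several stronger readings are tempting but unsupported:

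- *The test ignores baseline by comparing raw follow-up values.* The sentence says only clinical outcomes and does not specify level or change. For SF-12v2, the Secondary outcomes define the measure as a change.
- *Baseline values are already held for both groups on every outcome.* A control baseline is explicit only for the quality-of-life survey, which the stated between-group test does not cover. For clinical data it is implied at most. The section Potential to realize change says Kt/V sat in free text or on paper, with an optional field for HD-PPP patients.
- *Ignoring the matching is a serious error.* Subjects does not say that matching is pairwise, and if it is, the error is conservative (step 4).
- *The false-positive rate is far higher.* An imbalance of 0.5 SD would give 21% to 77% by the same formula, but nothing in the article supports an imbalance of that size.

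An unseen analysis plan is not a full answer either. The article does not leave the method open. It names one.

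**Conclusion.** The point holds as a badly fixed method for the control comparison. As written, the test cannot separate a programme effect from differences in who enrolled, and the PRO side of the third hypothesis has no stated between-group test. Confounding is the main harm, clustering is second and matching is minor.

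Under the assumed inputs, the false-positive rate is about 7.5% to 37% for a modest baseline imbalance, and about 6% to 18% for clustering alone. These ranges are illustrative: only the counts 120, 7 and 15 come from the article. They describe a generic standardised outcome, not Kt/V or haemoglobin specifically.

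A reader might infer that the whole evaluation is compromised. It is not. The primary outcomes are proportions meeting preset standards, reported descriptively, and the control comparison serves one of three hypotheses. The change should be made, but the study's main audit findings do not depend on it.

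**What to change.** Make the main between-group analysis a regression: linear for continuous outcomes, logistic for Kt/V adequacy. State that it covers PROs as well as clinical outcomes.

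- **Covariates:** age, gender, weekly HD sessions and entry route, plus dialysis vintage and comorbidity if the hospital authority's extract holds them. The article does not say that it does.
- **Baseline value of the outcome where it exists:** SF-12 and KDQOL scores for both groups; Kt/V and haemoglobin where recorded. Do not require it for the enablement and global-change scales, which Evaluation on outcomes of care places in the follow-up surveys. Patients newly starting dialysis or coming from PD may have no HD baseline for Kt/V, so say how they are handled.
- **Site:** allow for clustering by treating site (community centre for HD-PPP, renal unit for controls) with a random effect or a small-sample cluster-robust standard error. Use the parent renal unit as the common factor. Community centres occur only in the HD-PPP group, so they cannot serve as simple strata.
- **Crude tests:** keep the t-test and chi-square results as description.

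The cost is analysis wording and a few more extract fields. Baseline Kt/V will be incomplete, and intervals may widen once clustering is allowed for. Adjustment removes only measured confounding, and the report should say so.

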**Methods/Design:**

This is a longitudinal study based on Action Learning and Audit Spiral methodologies to measure the achievement of pre-set target standards for the HD-PPP programme over three evaluation cycles. The QOC evaluation framework is comprised of structure, process and outcome criteria with target standards in each domain developed from review of the evidence and in close collaboration with the HD-PPP working group. During each evaluation cycle, coordinators of each study site complete a questionnaire to determine adherence with structural criteria of care. Process and clinical outcomes, such as adverse events and dialysis adequacy, are extracted from the patient records of consenting study participants while face-to-face interviews are conducted to ascertain patient-reported outcomes such as self-efficacy and health-related quality of life.

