### Trial status

The first two evaluation cycles have been completed resulting in a final QOC evaluation framework developed for use in the third evaluation cycle based on new and revised indicators and target standards. The third evaluation cycle began in April 2012 and data collection is ongoing.

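### Evaluation cycles are compared with independent-sample tests although continuing patients count in more than one cycle; this overstates the standard error and makes real change between cycles easier to miss

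*Protocol article*

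**What the plan says.** The Data analysis section lists four analyses. The fourth covers change from cycle to cycle: "Independent sample t-test or chi square test as appropriate will be used to compare the clinical outcomes between results achieved in different evaluation cycles". The second, on HD-PPP patients over time since enrolment, says that results "at baseline, 12, 24, 36 and 48 months will be compared by paired sample t-tests".

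The rest of the article describes one cohort followed through all three cycles:

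- Abstract, Methods/Design: "This is a longitudinal study based on Action Learning and Audit Spiral methodologies". The same paragraph says how outcomes are obtained in the cycles: "Process and clinical outcomes, such as adverse events and dialysis adequacy, are extracted from the patient records of consenting study participants".
- Subjects: the process evaluation takes in "All patients participating in the HD-PPP programme between 1 March 2010 and 30 June 2014", and the outcome evaluation "All HD-PPP participants and an equal number of non-HD-PPP participants".
- Evaluation on outcomes of care, which sets the yearly schedule: "Anonymized data on clinical parameters at baseline, 12, 24, 36, 48 and 60 months after enrollment will be retrieved from the CMS".
- Trial status: the first two cycles are complete. "The third evaluation cycle began in April 2012 and data collection is ongoing".

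No section limits a cycle to newly enrolled patients, and none mentions clustering or repeated measurement for the cycle comparison.

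**The concern.** The independent-sample t-test and the ordinary chi-square test treat the groups as made up of different people. A patient who enters in an early cycle and stays is in both groups. Values from one patient are normally positively correlated, and the variance of a difference between two positively correlated means is smaller than the independent formula assumes. The reported standard error is then too large.

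The section already treats repeated values on the same patients as paired when the time axis is months since enrolment. It drops that dependence when the same records are regrouped by cycle.

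According to the section on the three cycles, the third is meant to show whether standards of care are sustained. A test with too little sensitivity tends to return no significant difference, and that is easily read as evidence that standards held. The sentence covers clinical outcomes only. These include Kt/V, which the Discussion calls the primary clinical outcome indicator.

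**Working it through.** The article states no sample size, power or alpha for the cycle comparison, so there is no figure to reproduce.

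**Step 1: do the cycles share patients?** Inputs: programme participation from 1 March 2010 (Subjects), clinical values at 0, 12, 24, 36, 48 and 60 months (Evaluation on outcomes of care), start of cycle 3 in April 2012 (Trial status).

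- A patient enrolled in March 2010 has values due in March 2010, 2011 and 2012, before cycle 3, and in March 2013 and 2014, within cycle 3.
- A patient enrolled in March 2011 has values due in March 2011 and 2012 before cycle 3, and in March 2013 and 2014 within it.
- In general, anyone enrolled before April 2012 who stays has 2 to 3 scheduled values between April 2012 and 30 June 2014.
- The boundary between cycles 1 and 2 is not given. For each boundary tried, from month 3 to month 21 after 1 March 2010, some enrolment months give values in both cycles.

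So overlap follows from the schedule for every pair of cycles. Its extent does not: the Discussion gives 120 patients ever enrolled by 31 March 2012, but not how many stayed or how many cycle 3 contains.

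**Step 2: effect of overlap, one value per patient per cycle.** Let n patients be in each cycle, a share f common to both, with within-patient correlation rho and common variance s².

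- Variance assumed by the independent test: 2s²/n.
- True variance: 2s²(1 - f × rho)/n.
- Overstatement of the SE: R = 1/sqrt(1 - f × rho).
- Actual two-sided error at nominal 5%: 2 × (1 - Phi(1.96 × R)).
- Power for a difference that a test with the correct SE would detect with 80% power: Phi(2.80 - 1.96 × R), where 2.80 = 1.96 + 0.84.

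Both f and rho are assumptions.

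| f | rho | R | 1.96 × R | Actual error | Power (80% with correct SE) |
|---|---|---|---|---|---|
| 0.3 | 0.3 | 1/sqrt(0.91) = 1.05 | 2.05 | 4.0% | 77% |
| 0.6 | 0.5 | 1/sqrt(0.70) = 1.20 | 2.34 | 1.9% | 68% |
| 0.9 | 0.7 | 1/sqrt(0.37) = 1.64 | 3.22 | 0.1% | 34% |

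**Step 3: if repeated values in cycle 3 were counted as separate subjects.** The article does not say that they are. Take equal patient numbers, one value per patient in the early cycle, m values per patient in cycle 3, and no overlap. In units of s²/n, the assumed variance is 1 + 1/m and the true variance is 1 + (1 + (m - 1) × rho)/m.

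- m = 2, rho = 0.3: sqrt(1.65/1.50) = 1.05, actual error 6.2%.
- m = 3, rho = 0.7: sqrt(1.80/1.33) = 1.16, actual error 9.2%.

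**Step 4: both together.** With f = 0.5, rho = 0.5 and m = 2, the true variance is 1 + 0.75 - 2 × 0.5 × 0.5 = 1.25 and the assumed variance 1.50. The ratio of true to assumed SE is sqrt(1.25/1.50) = 0.91 and the actual error is 3.2%. In this example overlap outweighs the repeats.

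**The case against.** The strongest reply is that the cycle comparison is supporting. The hypotheses concern structure and process criteria, Kt/V adequacy at 12 to 48 months, and outcomes no worse than in controls; none is about a difference between cycles. The objectives compare observed with target standards, and change over time is also tested by paired t-tests. This stands. The cycle test is not the only inferential look at change, and that limits the severity. It remains the only test named for change between cycles, and sustainability is the stated focus of cycle 3.

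A second reply is that the size of the error cannot be fixed. This also stands. Retention is not given, and the Discussion reports that Kt/V was hard to retrieve, from free text or paper records or from an optional field, so usable early overlap may be low. At f = rho = 0.3 the error rate is 4.0%, a mild departure.

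A reader might go further and infer that false positives are heavily inflated because several yearly values per patient are pooled in both cycles being compared. The article does not support that. It never says that all yearly values enter as separate subjects, and the choice of record per cycle is a detail commonly left to the full protocol or analysis plan. The calendar also limits it: even the first enrolled patient has at most three scheduled values before April 2012, across both early cycles together.

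A reader might also object to a two-sample test for three cycles. Chi-square accommodates three groups and pairwise t-tests are legitimate, so that is not a separate error.

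**Conclusion.** The named tests do not fit the described cohort. Patients enrolled before April 2012 who remain belong to an early cycle and to cycle 3, and only disjoint patients per cycle would justify the independent-sample tests. Nothing in the article describes such cycles.

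With one value per patient per cycle, the error is conservative. The SE is overstated by a factor of about 1.05 to 1.64, and the actual type I error is about 4% to 0.1% at nominal 5%. This rests on equal patient numbers per cycle and on assumed f of 0.3 to 0.9 and rho of 0.3 to 0.7. The consequence is lost sensitivity to real change. Inflation to about 6% to 9% would arise only if 2 to 3 values per patient in cycle 3 were treated as separate subjects without cross-cycle overlap. That is a conditional warning, not something the plan states.

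Severity: should-fix.

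**What to change.** Replace the fourth analysis with one model per clinical outcome, with patient as the cluster and cycle as a three-level factor: a linear mixed model for haemoglobin, and a logistic GEE or mixed model for Kt/V adequacy. Use all patients observed in each cycle, and report the cycle contrasts with 95% confidence intervals. Such a model handles overlap between cycles and any repeated values within a cycle.

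Paired t or McNemar tests in patients present in both cycles should be secondary only. They leave out new entrants and everyone who died or left, so they answer a question about patients who stayed.

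The cost is a change of wording, slightly more programming, and a persistent patient code on each Hospital Authority extract. The planned paired tests already need patients to be linked over time, so anonymised extraction should not be an obstacle. No new measurements are required.
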